### Strategies to improve adherence to interventions {11c}

Intervention is a single procedure\ event and does not require repetition, therefore adherence is not a feature of intervention delivery.

### Relevant concomitant care permitted or prohibited during the trial {11d}

Prohibited concomitant care is the application of vesicants or irritants infusions through a peripheral vein cannula. Allowed concomitant care is antibiotics therapy which are not vesicants or irritants.

### Provisions for post-trial care {30}

The sponsor has insurance, which is in accordance with the legal requirements in Slovakia. There is no ancillary care. Only common, well-known complications can occur in relation to peripheral vascular access.

### Outcomes {12}

In order to achieve primary and secondary outcomes, the number of attempts, number of cannulas used, tip redirections, time needed to insert the cannula, and proportion of cannulas that requires reinsertion, all this is recorded in the study protocol (Fig. 2) during the procedure. Then researchers will compare both groups to each other. These outcomes are crucial to determine clinical efficacy not just on insertion, but to compare the service life of the cannula inserted. The lifespan of the cannula is related to site of insertion (flexion point), damage to the vessel wall (number of redirections, 1^st^ pass), and proportion of cannula width to vessel diameter. Risks of peripheral vein cannulation are well known and, in general, considered minor.

### Participant timeline {13}

**Table Tabb:** 

	Study period					
	Enrolment	List of patient time period	Allocation	Post allocation		Close out
Timepoint	Day − 1	Day – X	0	Day 1	Day 2–4	Day 5
Enrolment:						
Eligibility screen	X					
Informed consent	X					
Randomization		X				
Allocation			X			
Interventions:						
Group C				X		
Group USG				X		
Assessments:						
Baseline variables				X		
Primary outcome				X		
Secondary outcome					X	X

### Sample size {14}

The estimate for the final sample size was based on the expected drop-out rate and the objective and design of the study. This trial assumes a comparison of the effect on outcome variables in peripheral vein insertion in the USG group and palpation-inserted peripheral venous cannula as the control group. In overall, we hypothesize that it will take fewer attempts to insert the cannula into a vein with the USG technique (USG: 1 vs. C: 1–3), corresponding to a reduction in time of ≥ 3 min (clinically relevant indicator) for successful cannulation in the USG group. When calculating the sample size, based on our experience and literature data, we assumed a 20% risk of complications inserting the cannula into a vein in the standard way, 5% as a probability of a Type I error (α < 0.05), and the power of the test 90% (β = 0.10). Theoretically, we also accepted a 5% risk failure of a first insertion of a cannula into a vein in the USG group. The sample size calculation was based on the result of the risk ratio (RR) between groups as % of complications (unsuccessful prick) with cannula insertion into the peripheral veins [9]. The adequate sample size of 162 patients was calculated as described previously [10], increased by 20% for the case unforeseeable circumstances (technical error, data loss, poor patient cooperation, etc.) and rounded ≅ 200.

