## Statistical methods

### Statistical methods for primary and secondary outcomes {20a}

The primary and secondary outcomes will be evaluated using the *χ*^2^ test in terms of the difference in approaches of cannula insertion between groups in the number of punctures and the failure rate of the cannulas (failure rate is defined as the proportion of cannulas requiring reinsertion within 5 days after insertion). RR and 95% confidence interval of successful venous cannulation will be also calculated. The primary endpoint is the number of attempts to successful cannulation determined by the number of skin punctures. More attempts are associated with complications. As a secondary endpoint, the failure rate is calculated from the ratio of cannulas that did not fail to cannulas that failed for any reason in each group, up to the first 5 days postoperatively. This data is obtained from the patient protocol (Fig. 2). Primary and secondary outcomes will be reported as frequencies and percentages. For our tertiary outcome, to compare differences between the intervention groups (time required for cannula insertion, number of cannulas used, A-DIVA scoring system, etc.), *t*-test for independent groups or Mann–Whitney U test will be used, if data are not normally distributed. The effect of the intervention on outcome variables will be determined by using paired *t*-test or Wilcoxon signed-rank test for data obtained at baseline and for 5 days of the study. Other endpoints include portion of long PVCs that are able to ensure blood draw up to 5 days postoperatively, time needed to insert PVC in each group, reinsertion of PVC needed in both groups for any reason. All this data is recorded in the study protocol.

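### The stated 162 patients do not give 90% power for 20% versus 5% under the two-sided 5% analysis the plan implies; power there is about 83–85%, and 90% needs about 194–202 analysed

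*Protocol article*

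**What the plan says.** The Sample size section (item 14) gives every input of a two-proportion calculation:

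- Control arm: "we assumed a 20% risk of complications inserting the cannula into a vein in the standard way".
- Ultrasound arm: "we also accepted a 5% risk failure of a first insertion of a cannula into a vein in the USG group".
- Error rates: "5% as a probability of a Type I error (α < 0.05") and "the power of the test 90% (β = 0.10").
- Result: "The adequate sample size of 162 patients was calculated as described previously [10], increased by 20% for the case unforeseeable circumstances", then rounded to about 200.

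The section does not say whether alpha is one-sided or two-sided, and it gives no allocation ratio. The formula is left to a cited reference.

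The section on statistical methods for primary and secondary outcomes (item 20a) says that these outcomes "will be evaluated using the *χ*^2^ test in terms of the difference in approaches of cannula insertion between groups" and adds that "RR and 95% confidence interval of successful venous cannulation will be also calculated". No section announces a one-sided test.

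**The concern.** A chi-square test of a difference between groups has no direction, and a 95% interval corresponds to a two-sided 5% test. The sample size should therefore be a two-sided 5% figure. For 20% versus 5% with 90% power, 162 in total looks too small for that.

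Two statements are at stake. One is the headline claim that 162 patients deliver 90% power. The other is the purpose of the extra patients: the plan presents everything above 162 as cover for unforeseen loss. If about 200 is what 90% power needs in the first place, most of that cover is already spent.

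**Working it through.** **Inputs.** p1 = 0.20, p2 = 0.05, difference d = 0.15, alpha = 0.05, power = 0.90 (all from item 14). Two-sidedness is inferred from item 20a. Allocation of 1:1 is my assumption. The mean proportion is 0.125.

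Variance terms:
- pooled: 2 × 0.125 × 0.875 = 0.21875, square root 0.4677
- unpooled: 0.20 × 0.80 + 0.05 × 0.95 = 0.2075, square root 0.4555

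**Formulas, n per arm.**
- Pooled: n = (z_alpha × 0.4677 + z_beta × 0.4555)² / d²
- Unpooled: n = (z_alpha + z_beta)² × 0.2075 / d²

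Here z_beta = 1.2816 and d² = 0.0225.

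**Step 1: the plan's own figure.** With one-sided alpha 5% (z_alpha = 1.6449):
- Pooled: (0.7693 + 0.5838)² / 0.0225 = 81.4, so 82 per arm, 164 in total.
- Unpooled: 2.9264² × 0.2075 / 0.0225 = 79.0, so 79 per arm, 158 in total.

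The stated 162 (81 per arm) lies between these. One-sided power at 81 per arm is 89.9%.

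**Step 2: two-sided alpha 5%** (z_alpha = 1.9600):
- Pooled: (0.9167 + 0.5838)² / 0.0225 = 100.1, so 101 per arm, 202 in total.
- Unpooled: 3.2415² × 0.2075 / 0.0225 = 96.9, so 97 per arm, 194 in total.

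Other two-sided formulas at 90% power give 186 (arcsine), 206 (simple pooled), 228 (continuity-corrected), 238 (log odds ratio) and 252 (log risk ratio). None gives 162. Allocation of 1:2 or 1:3 does not give it either, with one-sided or two-sided alpha.

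**Step 3: two-sided power at the relevant sizes.** Normal approximation: power = Φ[(d × √n − 1.9600 × 0.4677) / 0.4555]. At n = 81 this is Φ[(1.3500 − 0.9167) / 0.4555] = Φ(0.951) = 82.9%. The exact column sums binomial probabilities over all outcomes that an uncorrected Pearson chi-square test rejects.

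| Analysed (per arm) | Situation | Normal approximation | Exact Pearson |
|---|---|---|---|
| 200 (100) | no loss | 90.0% | 92.1% |
| 190 (95) | 5% of 200 lost | 88.4% | 90.7% |
| 180 (90) | 10% of 200 lost | 86.7% | 89.0% |
| 162 (81) | stated adequate size | 82.9% | 85.4% |
| 160 (80) | 20% of 200 lost | 82.5% | 84.9% |

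The more conservative Fisher test, which is not the one planned, gives 79.9% at 81 per arm and 88.3% at 100 per arm.

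**The case against.** **The practical effect may be small.** The primary outcome is the number of skin punctures, noted during the procedure, and the participant timeline places it on the day of the intervention. Allocation is opened in the block room on the day of surgery, and the retention section (item 18b) calls exclusion unlikely. A 20% loss on this outcome is a worst case. With little loss, 200 enrolled patients meet the 90% target under a two-sided test. This stands, and it limits the harm to the trial. It does not make 162 adequate for 90%.

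**Some reserve does exist.** A reader might infer that 90% power needs every one of the 200 patients. The exact power of the planned chi-square test does not support that: it is 92.1% at 200 and still 90.7% at 190. A reserve of about 5% is there; one of 20% is not.

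**The source of 162 is unknown.** A reader might conclude that the authors ran a one-sided calculation. That is the best-fitting explanation, but the pooled formula rounds up to 164 and the unpooled one gives 158. Neither is exactly 162, and the cited method is not at hand. The documents support only the narrower statement that standard two-sided formulas at 90% power do not give 162.

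**The inflation step.** A reader might also object that 162 was multiplied by 1.2 rather than divided by 0.8. The plan says it raised the number by 20%, and 162 × 1.2 = 194.4 does that. After 20% loss from 200, 160 remain instead of 162, which moves power by about 0.4 percentage points. This does not merit a separate point.

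**Conclusion.** The pairing of 162 patients with 90% power is wrong as written for the analysis described. Two-sided power at 162 is about 83–85%, so the Type II error is about 15–17% instead of 10%. The shortfall against the two-sided requirement is 32 to 40 analysed patients (194 − 162 and 202 − 162).

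The enrolment target itself is sound at the stated power if losses are small. The defect lies in the stated basis for that target and in the size of the reserve, not in the number to be enrolled.

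The conclusion rests on three assumptions: the analysis is two-sided, as the chi-square test and the 95% interval imply, though the plan never says so; allocation is 1:1; and the 20% and 5% are the failure proportions to be compared. The 83–85% range covers the normal approximation and the exact uncorrected Pearson test.

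**What to change.** Keep 200. In item 14, state the sidedness and the allocation ratio, delete the claim that 162 is adequate for 90% power, and write:

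> With two-sided alpha 5%, 1:1 allocation and failure of 20% vs 5%, 200 analysed patients give about 90% power; with 20% loss (160 analysed) power is about 82–85%.

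If a one-sided calculation was in fact used, only the authors can confirm that from their own records.

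The cost is one reworded paragraph. No patients are added and the planned test does not change. The price is a less favourable stated power if losses reach the full allowance.

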### Recruitment {15}

The study will include all patients who are indicated for surgery at the time of the registration period and who have met the agreed inclusion criteria. Under the sponsor’s supervision, investigators initiate patient’s enrolment. In our institution, 1.000 arthroplasties are performed annually. The intervention is low cost and necessary to conduct surgery.

## Assignment of interventions: allocation

### Sequence generation {16a}

A random sequence of numbers is generated using SPSS software v. 20.0 (IBM SPSS, Armonk, NY), and this is translated to a series of opaque envelopes which will be used to allocate eligible participants to groups once they have satisfied the inclusion criteria. On the day of surgery, in the block room, the anesthetist will open the envelope and find out the allocation of the patient. According to patient allocation, medical staff will perform the procedure in accordance with the study protocol. This procedure will be repeated until the target sample size is reached.

### Concealment mechanism {16b}

Only one employee working with randomization has knowledge about patient allocation. Each patient allocation is in a sealed opaque envelope. On the day of surgery, in the block room, the anesthetist will open the envelope and find out the allocation of the patient. According to patient allocation, medical staff will perform the procedure in accordance with the study protocol.

### Implementation {16c}

Allocation sequence will be generated by SPSS. Participant enrollment is up to the anesthetists and orthopedic surgeons. Allocation is not concealed and will be revealed to both the patient and the researcher upon randomization.

## Assignment of interventions: blinding

### Who will be blinded {17a}

It is almost impossible to blind care providers or patients because of different appearances of cannulas and different fixation of devices. There is no blinding.

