### Trial design {8}

This investigator-initiated prospective randomized parallel groups monocentric controlled trial is designed to enroll 200 patients. There is no blinding because cannulas are easy to distinguish.

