### Procedure for unblinding if needed {17b}

Not applicable. There is no blinding.

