### Plans to promote participant retention and complete follow-up {18b}

Participants are studied only up to 5 days or discharge from the hospital, whichever comes first. The study doesn’t require any extra actions or active collaboration from patients. If the patient deviates from intervention protocols, we will use data of the patient up to the timepoint of deviation if eligible; if not, the patient will be excluded. Exclusion probability is low due to the short period of observation and low to none patient active collaboration.

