### Methods in analysis to handle protocol non-adherence and any statistical methods to handle missing data {20c}

Not all processes set up in the study deviate from the design of the randomized controlled clinical trial. When analyzing data, if any qualitative or metric data is found, we will first contact a team member who records or measures the data to supplement the missing data, if at all possible, while analyzing the reasons why the data is missing. We will use all available SPSS applications to check/analyze data completeness. In addition, SPSS statistical programs can evaluate and process incomplete data sets correctly (each analysis uses only cases without missing values for all variables and for all analyses). Therefore, we will not artificially attribute any missing values and we will take into account the missing data in the interpretation of the results. Patients with a large amount of missing data will be excluded from the final statistical analysis.

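### The reason given for having no blinding does not cover whoever decides exclusions or runs the primary and secondary analyses; those steps can be done on coded arms at little cost

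*Protocol article*

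**What the plan says.** The protocol article states in three places that nobody is blinded. Trial design {8}: "There is no blinding because cannulas are easy to distinguish". Item 17a says that patients and care providers can hardly be masked, and gives as its ground "different appearances of cannulas and different fixation of devices. There is no blinding". Item 17b, on breaking the blind, adds: "Not applicable. There is no blinding".

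Three later rules need judgement:

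- Missing data {20c}: "Patients with a large amount of missing data will be excluded from the final statistical analysis". No amount is given.
- Deviations {18b}: "we will use data of the patient up to the timepoint of deviation if eligible; if not, the patient will be excluded". What makes a patient eligible is not defined.
- Statistical methods {20a}: for tertiary metric outcomes, a t-"test for independent groups or Mann–Whitney U test will be used, if data are not normally distributed". No criterion for normality is given.

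The same section {20a} fixes the chi-square test for the primary outcome (attempts, counted as skin punctures) and the secondary outcome (cannula failure up to 5 days). Patients are identified by numerical codes (Confidentiality {27}), data are entered into a spreadsheet (Data management {19}), and a data manager is named among the trial roles {5d}.

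**The concern.** The stated reason is narrower than the decision it supports. How a cannula looks on the arm explains why the patient and the inserting physician cannot be masked. It says nothing about a person who sees rows of codes and values, and the article gives no other reason for leaving that person unmasked.

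This matters because item 20c describes exclusions from the final analysis that depend on case-by-case judgement, and item 18b adds a second undefined rule. In a trial declared wholly open, whoever applies these rules may know the arm and therefore the direction in which each exclusion moves the result. Few failures are expected under ultrasound: at the planned 5% risk and 100 patients per arm, about 5. A single exclusion can therefore carry weight. The trial also has no data monitoring committee {21a} and no steering committee {5d}, so neither body stands between knowledge of the arm and these decisions.

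**Working it through.** **Passages side by side.** Item 17a names two groups that cannot be blinded, care providers and patients, and then concludes that there is no blinding at all. Item 8 gives the same ground. The analysis stage appears in neither. The rules in 18b and 20c decide who is in the analysis set, so they reach the primary outcome. The normality rule in 20a does not, because the primary and secondary tests are already fixed.

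**Inputs.** The plan gives no figure on this point, so the size has to be illustrated.

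- Sample size {14}: 162 × 1.2 = 194.4, rounded to 200. I assume equal arms, 100 each.
- Planned first-insertion failure {14}: 20% by palpation, 5% with ultrasound.
- Assumption: the primary outcome is reduced to first-puncture failure, yes or no, as the sample size calculation does.
- Assumption: with no true difference, the common risk is the midpoint (20% + 5%)/2 = 12.5%. I also show 5% and 20%.
- Two-sided 5% level, Pearson chi-square without continuity correction: z = (x1/n1 − x2/n2) / √[p(1−p)(1/n1 + 1/n2)], with p = (x1+x2)/(n1+n2).

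**Step 1: one exclusion at the boundary.**

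- 14/100 palpation against 6/100 ultrasound: p = 20/200 = 0.100; z = 0.080/0.0424 = 1.886; P = 0.059.
- One ultrasound failure removed, 14/100 against 5/99: p = 19/199 = 0.0955; z = 0.0895/0.0417 = 2.148; P = 0.032.

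**Step 2: false wins when there is no difference.** I summed the exact binomial probabilities of every pair of failure counts (100 per arm, same risk) for which the test is significant in favour of ultrasound after k ultrasound failures are removed.

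| Common risk | k = 0 | k = 1 | k = 2 | k = 3 |
|---|---|---|---|---|
| 5% | 2.2% | 6.1% | 13.7% | 24.7% |
| 12.5% | 2.6% | 4.2% | 6.6% | 10.3% |
| 20% | 2.6% | 3.7% | 5.2% | 7.1% |

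**Step 3: the planned scenario.** With exactly 20/100 against 5/100: p = 25/200 = 0.125; z = 0.150/0.0468 = 3.207; P = 0.0013. Removing one ultrasound failure changes no conclusion here. Over all possible results at true risks of 20% and 5%, removing one ultrasound failure turns a non-significant result into a significant one in about 3% of trials.

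**Step 4: would coded arms stay masked?** At the planned rates the palpation arm shows more failures than the ultrasound arm with probability 99.9% (exact binomial, 100 per arm). A file that contains attempt counts would therefore suggest the arms as soon as A and B are compared. Exclusions have to be settled before outcome values are seen.

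**The case against.** The strongest reply is that the room for bias comes from the undefined rules, not from the missing mask. On that view, fixing the thresholds in advance would remove the discretion directly, and an analysis plan that is not shown may do so. This stands in part: thresholds are desirable, and their absence from an article is not the point here. A decision on whether a deviating patient remains eligible would still be a case judgement, and the article's statement that there is no blinding is a positive one, not a detail left to another document.

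Second, the figures are a worst case. They assume that every removed patient is an ultrasound failure. Item 20c removes only patients with much missing data, after an attempt to recover it. Attempts are noted by another researcher during one procedure {11a}, and item 18b calls exclusion unlikely. This stands. A reader might infer that an analyst could delete complete records of failures. The documents do not allow that, and they do not say who decides exclusions.

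Third, a reader might infer that the open choice between t-test and Mann–Whitney lets the primary result be steered. It does not: that choice concerns tertiary outcomes only.

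Fourth, masking would be incomplete. Attempt counts would suggest the arm (step 4), and blood draw is defined for long cannulas only {20a}. Study personnel have access to the study documents {18a} and enter the forms themselves {19}, and no statistician is named among the roles in 5d. This stands, and it shapes the fix.

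**Conclusion.** The point holds in a limited form. The ground for no blinding covers patients and care providers only, while two judgement-based exclusion rules that can affect the primary result are to be applied with nothing in the article to hide the arm. That these exclusions are made at analysis is inferred from the wording of 20c; the article names no decision-maker.

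The plausible effect is modest. Under an assumed common risk of 12.5% and 100 per arm, one to three fully selective removals raise the false-win rate for ultrasound from 2.6% to 4.2–10.3%. Three removals give 7.1% at 20% risk and 24.7% at 5%. These are upper illustrations, not predictions.

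The documents do not support saying that full masking is available or free. Partial masking at the exclusion step is cheap and worth having. It leaves untouched the open recording of attempts and failures, which is a separate route to bias.

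**What to change.** Amend items 8 and 17a to say that participants and care providers are not blinded, and that exclusions and the primary and secondary analyses are carried out on coded arms. Then:

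1. The data manager prepares a file without arm label, device fields or outcome values. It holds only missingness flags and descriptions of deviations, stripped of detail that reveals the arm.
2. Exclusions are decided on that file, and the decision is dated.
3. For tertiary metric outcomes, the choice of test is made on distributions that are pooled or coded A/B, before the code is broken.
4. The primary and secondary chi-square analyses are run with arms coded A/B, and the code is broken afterwards.

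Item 17b then needs one sentence on when the code is broken.

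Cost: a recoded file and a dated note, using a role that already exists. Sample size, significance level and power do not change. Masking remains partial, because outcome differences may suggest the arm once the analysis starts.
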